Previous studies on the relationship between obesity and precocious puberty have mostly been cross-sectional studies, with few studies on pleiotropic genes of obesity and puberty. To explore the relationship between obesity and puberty development, this prospective cohort study will investigate the genetic, parental, social and family environment, lifestyle, and other determinants of puberty development. This protocol describes an overview of the design and methods of this cohort study, which is funded by the National Natural Science Foundation of China (grant number 81872637). The study objectives are as follows: I) analyzing the incidence of precocious puberty in the general population in China, examining the direct effect of childhood obesity on precocious puberty; II) exploring the relationship between prepuberty obesity and its risk genes and precocious puberty; III) determining the relationship between prepuberty obesity and its risk genes and hormone levels among children with precocious puberty; and IV) analyzing the interaction effect between genes and environmental factors on precocious puberty.

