#### Sample size

Based on the formula for calculating the sample size of a cohort study at one-side significance level: [22].$$N={\left[\frac{u_{\alpha}\sqrt{2\overline{p}\left(1-\overline{p}\right)+}{u}_{\beta}\sqrt{p_1\left(1-{p}_1\right)+{p}_2\left(1-{p}_2\right)}}{p_1-{p}_2}\right]}^2$$

According to the previous studies, the prevalence of precocious puberty was 4.85% (*P*_2_) and 8.43% (*P*_1_) of children aged 7–10 years with normal weight and overweight, respectively [12, 23]. A type I error (*α*) of 0.05, u_0.05_ = 1.96;, β = 0.10, u_0.10_ = 1.28; and a loss of follow up rate of 15%, a total of 4152 children will be required in each center. Finally, inverse-variance weighting (IVW) methods will be used to adjust the sample size.

Based on the SNP gene differences between different groups reported in the literature, Quanto 1.2.4 software (John Morrison, W. James Gauderman 2009, University of Southern California) was used to estimate sample sizes for each group. According to the previous pre-experimental results of obesity study showed that the allele frequency was 0.30 and the minimum allele frequency (MAF) was 0.10 using Additive Genetic Model (ADD), the type I error (α) of 0.05, the actual Power is 0.80, we need average of 800 participants per group and 3200 cases for four groups. Cases among four groups will be controlled by sex and age.

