### Data collection

#### Genotyping and SNP selection

Due to differences in gene polymorphism distribution in different ethnic groups, we screened ten candidate genes and selected one or two representative single-nucleotide polymorphisms (SNPs) each gene on the basis of the Hans according to GWAS database (www.genome.gov/gwastudies) and the related literatures, the candidate genes and SNPs were shown in Table 2.

**Table 2 Tab2:** The characteristics of candidate gene associated with obesity and precocious puberty

Gene	Chr	SNP1	SNP2
*ADCY3*	2p23.3	rs6752378	rs713586
*BDNF*	11p14.1	rs4923461	rs7481311
*FTO*	16q12.2	rs1121980	rs1558902
*KCTD15*	19q12.1	rs29941	rs287103
*LEP*	7q32.1	rs104894023	rs724159998
*NEGR1*	1p31.1	rs2568958	rs2815752
*SEC16B*	1q25.2	rs10913469	rs543874
*TMEM18*	2p25.3	rs4854344	rs2867125
*TNNI3K*	1p31.1	rs1040070	rs1514175
*MC4R*	18q22	rs663129	rs12970134

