### Data analysis

Categorical variables will be reported as the number and percentage and analyzed by a chi-square test to compare the distribution between groups. The *t*-test, analysis of variance, and Wilcoxon rank-sum test will be used to compare the differences in distribution of continuous variables, which will be described by mean ± standard deviation (*SD*) for normal data or median with interquartile range for non-normal data.

Based on the discovered pleiotropic genes and obesity-related risk loci (SNPS), we will examine the distribution of gene polymorphisms (SNPS). For obesity-related SNPs of these genes, Effect size Weighting was carried out according to the method reported by Speliotes EK et al. [40], and then genetic risk scores (GRS) will been calculated using the method established in our previous study [41].That is, the number of effective Allele genes (Allele) was calculated, then the weighted value was multiplied, and finally the combined GRS of SNPs of all candidate genes in this study was accumulated.

The effects of exposure factors on outcomes will be evaluated after adjusting confounding factors using logistic regression or multiple linear regression. To analyze whether there is a linear trend of GRS among four groups: children with normal weight and normal puberty, with normal weight and precocious puberty, with overweight/obesity and normal puberty, and with overweight/obesity and precocious puberty, the Cochran–Mantel–Haenszel Trend Test will be used. After 3 years’ follow-up, a causal relationship model between exposure factors and outcomes will be established by using Mendelian randomization (MR) and Egger’s regression models and assessed by sensitivity analysis. Statistical analyses will be performed by using IBM SPSS, STATA and R statistical packages. and the level of significance will be set at *p* < 0.05.

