At the same time, this study adopts several new analysis techniques, such as Mendelian randomization and Egger’s test, to verify potential pleiotropic genes and further identify the mediating role of obesity in the relationship between pleiotropic genes and precocity. There is a lack of understanding of the direction and extent of the effect of life behaviors and habits on the internal rhythm and timing of puberty and how external factors interact with genetics to influence the indicators of adolescent development, such as secondary sexual characteristics development and sex hormone levels. Through these analysis methods, we can understand the direct and indirect effects of these influence factors on child growth and development.

This study has several limitations that should be considered. First, information on the diets and physical activity of children will be collected through parent reports, which may lead to bias due to a lack of information on children’ behaviors at school. Second, detection of the number of genes and SNP is limited by research funding, and there can be differences in gene polymorphism distribution in different ethnic groups; therefore, we are basing our analysis on Han people according to the GWAS directory database (www.genome.gov/gwastudies) and literature reports on potential candidate genes to screen pleiotropic genes related to obesity and precocious puberty. However, only 2 SNPs per candidate gene will be tested in this study. Despite these limitations, China is a country of great ethnic and genetic diversity. Up to now, there have been few prospective cohort studies on obesity and puberty development in China. Through this multicenter prospective population-based cohort study, we expect to find that obesity and the external environment indeed have an impact on puberty development in Chinese children. It is possible to develop directional intervention measures on the basis of the established evidence for youth at risk in families, communities, or schools to improve the adolescent health.

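### Twenty candidate SNPs share one uncorrected 0.05 threshold with no lead genetic test: a 40% to 64% chance of at least one false-positive SNP under the global null, and a stated power of 0.80 that belongs to a single uncorrected SNP test

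*Protocol article*

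**What the plan says.** Under Genotyping and SNP selection the article reports that "we screened ten candidate genes and selected one or two representative single-nucleotide polymorphisms (SNPs) each gene". Table 2 gives two SNPs for every gene, so 20 in all, and the limitations paragraph of the Discussion confirms that two per gene will be tested.

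The aims are partly confirmatory. The Abstract's third objective is to verify the effect of obesity and its risk-gene polymorphism on precocious puberty. The fourth objective in the Background is "analyzing the interaction effect between genes and environmental factors on precocious puberty".

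Data analysis describes examining the distribution of the SNPs, building one weighted GRS over all candidate SNPs, a trend test of the GRS across four groups defined by weight and puberty status, logistic or linear regression, and Mendelian randomization with Egger regression. It closes with one threshold for the analyses: "the level of significance will be set at *p* < 0.05".

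The second part of Sample size sizes the genetic study with Quanto under an additive model, with "the type I error (α) of 0.05, the actual Power is 0.80", and concludes that "we need average of 800 participants per group and 3200 cases for four groups".

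**The concern.** A candidate-gene study that tests 20 SNPs, each at 0.05, expects 20 x 0.05 = 1 false-positive SNP per outcome and contrast even when none has an effect. That is tolerable if the SNP results are labelled a screen, or if one genetic test is named in advance and the rest are controlled. The article does neither, while one of its objectives is worded as verification. A SNP at, say, p = 0.03 could be reported as a pleiotropic gene although one such result among 20 is unremarkable.

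The sample size has the same root. Quanto was run at alpha 0.05. If the analysis later adopts any control over the SNP family, the stated 0.80 no longer describes the tests that are actually made.

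**Working it through.** **Inputs from the article.** Tests: 20 SNPs in ten genes (Table 2). Threshold: 0.05 (Data analysis). Genetic sample size: 800 per group, alpha 0.05, power 0.80, additive model, allele frequency 0.30 and minimum 0.10 (Sample size). Not stated: the odds ratio per allele, the contrast (which groups are compared) and whether the genetic calculation is one- or two-sided. Two-sided is assumed below.

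**Step 1: the plan's own figure.** The 800 per group cannot be reproduced, because the effect is given only as "Based on the SNP gene differences between different groups reported in the literature". One can solve for it. Treat the additive test as a comparison of allele proportions with 2 x 800 = 1600 alleles per group, where the case proportion is p1 = p0·OR / (1 − p0 + p0·OR). Power of 0.80 at two-sided 0.05 then requires:

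- OR about 1.36 if p0 = 0.10
- OR about 1.24 if p0 = 0.30

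Either way, this is one SNP, one 800 v 800 contrast and no correction.

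**Step 2: false positives among the SNP main effects** (global null, one outcome, one contrast). With m independent tests, the chance of at least one false positive is 1 − 0.95^m.

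| Assumption | Effective tests | Chance of at least one |
|---|---|---|
| Two SNPs of each gene fully correlated | 10 | 1 − 0.95^10 = 0.401 |
| All SNPs independent | 20 | 1 − 0.95^20 = 0.642 |

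Simulated correlations of 0.5, 0.8 and 0.95 within each gene pair give 0.615, 0.555 and 0.486, inside these bounds.

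**Step 3: interactions.** The article fixes no number of gene-by-environment tests, so no rate can be attributed to the plan. As an illustration only, one interaction test per SNP with a single exposure would make 40 tests, and 1 − 0.95^40 = 0.871 if all were independent.

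**Step 4: power at a corrected level** (illustration). An effect sized for 0.80 at two-sided 0.05 has noncentrality 1.960 + 0.842 = 2.802. The critical value is 3.023 at 0.05/20 = 0.0025 and 2.807 at 0.05/10 = 0.005.

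| Contrast | Noncentrality | Power at 0.0025 | Power at 0.005 |
|---|---|---|---|
| 800 v 800 | 2.802 | Φ(2.802 − 3.023) = 0.41 | Φ(2.802 − 2.807) = 0.50 |
| 1600 v 1600 (both weight strata pooled, same effect in each) | 2.802 × √2 = 3.962 | Φ(3.962 − 3.023) = 0.83 | Φ(3.962 − 2.807) = 0.88 |

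To keep 0.80 in the 800 v 800 contrast, about 1523 per group would be needed at 0.0025 and about 1358 at 0.005.

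**The case against.** **This belongs in the analysis plan.** Control of secondary SNP tests is often left there, and a 0.05 threshold can be read against adjusted p-values. That is fair as far as omission goes. But the article does fix something: one threshold for all analyses, and a sample size computed at that same alpha. A correction added later would leave the stated 0.80 without support.

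**The GRS already solves it.** The GRS is one test and is unaffected, as is the primary outcome, the incidence of precocious puberty by weight status. But the article neither makes the GRS the lead test nor says that it replaces SNP-level inference, and a score summed over ten genes cannot say which gene is pleiotropic.

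**The SNP work is a screen.** The limitations paragraph does speak of screening candidate genes. And where the Discussion says its methods are meant "to verify potential pleiotropic genes and further identify the mediating role of obesity", that sentence refers to Mendelian randomization and Egger's test, so it should not be read as a claim about 20 single-SNP tests. The confirmatory wording that does bear on the SNPs is the Abstract's third objective.

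**Four stronger readings should be resisted.**

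- *That the plan will more often than not name a false gene.* The main-effect range starts at 40%, so this does not follow. All the rates also assume the global null, while the Background reports MC4R, a Table 2 gene, as already related to precocious puberty.
- *That interactions push the rate to some definite figure.* Any such figure depends on a number of tests that the reader supplies. GRS-by-environment tests would fit the objective equally well.
- *That a SNP with p between 0.0025 and 0.05 fails under every family-wise method.* After one rejection, Holm tests the next SNP at 0.05/19 = 0.0026 and relaxes further. A max-T procedure with fully correlated pairs has a threshold near 0.005.
- *That true power is 0.41.* It holds only for an 800 v 800 contrast at exactly the sized effect. The pooled contrast gives 0.83. If 800 was sized at allele frequency 0.10 (OR about 1.36), a SNP at 0.30 with the same odds ratio has about 0.86 at 0.0025 even with 800 v 800.

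**Conclusion.** The point holds for SNP-level inference. As written, 20 SNPs are to be tested at 0.05 without a lead genetic test, multiplicity control or exploratory label, under an objective worded as verification. The chance of at least one false-positive SNP is about 40% to 64%, that is 8 to 13 times the nominal 5%. This is for one outcome and one contrast under the global null, and the range is set by the unknown correlation between the two SNPs of a gene. Interaction tests would raise it by an amount that the article does not allow one to compute.

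The 0.80 power is stated at the level for a single uncorrected SNP test. How far it falls under correction cannot be settled, because contrast and odds ratio are not given: the illustrations run from 0.41 to 0.88. Nothing here shows that 800 per group is wrong, and neither the GRS test nor the primary comparison is in question. The change should be made, but the study's main result does not depend on it.

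**What to change.** In Data analysis:

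1. Name the pre-weighted GRS against precocious puberty as the confirmatory genetic test at 0.05.
2. Test the 20 SNPs as one family with a stated method: Holm, Benjamini-Hochberg, or a permutation max-T that uses the within-gene correlation. Say whether family-wise error or false discovery rate is controlled.
3. Name one GRS-by-environment interaction in advance and label all SNP-by-environment tests exploratory.
4. Reserve the language of verification for results that survive this control.

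In Sample size, say that 0.80 applies to a single SNP at alpha 0.05. Restate power at the corrected level together with the contrast, allele frequency, odds ratio and sidedness used. The illustrative figures above should not be copied in as the study's power; the sponsor's own inputs should replace them.

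The cost is a few sentences, a routine p-value adjustment and a rerun of the power calculation, with no new data or participants. The downside is lower power for single-SNP claims.

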## Discussion

In this protocol, we described the study design, data collection methods, and analysis of a prospective cohort study in a population-based primary school children. According to the geographical distribution, we chose three cities in northern, central, and southern China and did our best to carry out this study to ensure the representativeness of the population. Students in grades 1 to 3 in randomly selected primary schools are expected to represent local school-age children.

By collecting information on factors such as children’s family environment, lifestyle, and genes, this study will analyze the effect of these factors on children’s physical development from the perspectives of heredity and environment. As a longitudinal study, this study will start earlier in development than previous studies to capture the impact of early childhood experiences on puberty development. Puberty is defined through visual and palpation inspection by a clinical doctor combined with ultrasonic diagnostics; previous studies have depended on self-reports or clinical palpation by non-professional volunteers, which are less sensitive and precise measurements, especially for breast development assessment among obese girls, which may lead to overestimating the precocious puberty detection rate among obese girls, since it is difficult to distinguish adipose tissue and breast tissue, so we will use ultrasonic examination in this study. Although the relationship between obesity and the sexual development of children has been confirmed in both genders by many earlier studies, due to the racial differences in the influence of obesity on sexual precocity, the relationship between obesity and early development is controversial among boys. Through this prospective cohort study, we will further investigate the relationship between obesity and development among Chinese mainland children.

To expand the previous research on puberty development, this study starts from the gene pleiotropy of obesity and takes the lead in studying the influence of the genetic polymorphism of obesity on precocious puberty. Although studies on genetic polymorphism of obesity or precocious puberty in girls have been performed previously, there has been no report on the combination of the two phenotypes, which is expected to reveal the genetic mechanism of the association between childhood obesity and precocious puberty.

At the same time, this study adopts several new analysis techniques, such as Mendelian randomization and Egger’s test, to verify potential pleiotropic genes and further identify the mediating role of obesity in the relationship between pleiotropic genes and precocity. There is a lack of understanding of the direction and extent of the effect of life behaviors and habits on the internal rhythm and timing of puberty and how external factors interact with genetics to influence the indicators of adolescent development, such as secondary sexual characteristics development and sex hormone levels. Through these analysis methods, we can understand the direct and indirect effects of these influence factors on child growth and development.

This study has several limitations that should be considered. First, information on the diets and physical activity of children will be collected through parent reports, which may lead to bias due to a lack of information on children’ behaviors at school. Second, detection of the number of genes and SNP is limited by research funding, and there can be differences in gene polymorphism distribution in different ethnic groups; therefore, we are basing our analysis on Han people according to the GWAS directory database (www.genome.gov/gwastudies) and literature reports on potential candidate genes to screen pleiotropic genes related to obesity and precocious puberty. However, only 2 SNPs per candidate gene will be tested in this study. Despite these limitations, China is a country of great ethnic and genetic diversity. Up to now, there have been few prospective cohort studies on obesity and puberty development in China. Through this multicenter prospective population-based cohort study, we expect to find that obesity and the external environment indeed have an impact on puberty development in Chinese children. It is possible to develop directional intervention measures on the basis of the established evidence for youth at risk in families, communities, or schools to improve the adolescent health.

### Study status

Enrollment of prospective longitudinal study participants had begun in October 2019. However, due to the COVID-19 epidemic, our investigation in different city cannot carried out simultaneously. Currently (as of April 2022), data collection of baseline survey in Zhongshan, Guangdong province and Qufu, Shandong province were done in December 2020, and the first year follow-up in two of above cities were finished in January 2022. Data collection and the analysis of the results is ongoing. The baseline survey in Dalian, Liaoning province is scheduled to begin in December 2022. The baseline characters of this survey in Zhongshan, Guangdong province and Qufu, Shandong province were summarized in Table 3.

**Table 3 Tab3:** The basic characteristics of the subjects in Qufu and Zhongshan

Category	Girls	Boys	Total
	3993 (%)	4630 (%)	8623 (%)
**Age (years)**			
6 ≤ age<8	2365 (59.23)	2821 (60.93)	5186 (60.14)
8 ≤ age<11	1628 (40.77)	1809 (39.07)	3437 (39.86)
**Districts**			
Urban	3151 (78.91)	3518 (75.98)	6669 (77.34)
Suburban	842 (21.09)	1112 (24.02)	1954 (22.66)
**Weight status**			
Thinness	720 (18.04)	629 (13.59)	1349 (15.64)
Normal weight	2594 (64.96)	2801 (60.50)	5395 (62.57)
Overweight or obesity	679 (17.00)	1200 (25.91)	1879 (21.79)

## Data Availability

The datasets used and/or analyzed during the current study are available from the corresponding author on reasonable request.

## Abbreviations

BMI: Body mass index
TV: Testicular volume
B: Breast
PH: Pubic hair
FSH: Follicle-stimulating hormone
LH: Luteinizing hormone
E _2_: Estrogens
T: Testosterone
EED: Environmental endocrine disruptors
SD: Standard deviation
PDS: Pubertal Development Scale
GRS: Genetic risk score
MR: Mendelian randomization
SNP: Single-nucleotide polymorphism
